Three systematic reviews have looked at benefits achieved by means of meals-on-wheels offered to older adults [13–15]. Home-delivered meal programs improve diet quality and increase nutrient intakes among participants [13]. However, more research is needed to evaluate the efficacy and effectiveness of home-delivered meals for older adults on multiple outcomes [14]. Very few randomized controlled studies have assessed the beneficial effect of meals-on-wheels as a supportive intervention [15]. In addition, no randomized controlled intervention studies have been investigating rehabilitation related to limitations of “Activities of daily living” (ADL) e.g. cooking, has any beneficial effect [16].

Support at home such as meals-on-wheels means becoming accustomed to a new mealtime experience. E.g. when still able to cook older adults often hold some control over the foods that are prepared and which they eat, and which helps to foster identity. Foods prepared at home are familiar to the person, holding memories of the past and as well, the activities of grocery shopping, meal planning, and food preparation may help to preserve social, cognitive, and functional abilities.

In this pilot trial, the primary research aim is to explore the community-dwelling older adults acceptability and feasibility of the outcome measurements as methods to measure efficacy of the intervention, and to provide data to estimate the required sample size for a future cluster randomized study of community-dwelling older adults being involved in their own meals in a rehabilitation program.

The second aim of this study is to perform a pilot cluster randomized trial to understand, on an individual level, whether community-dwelling older adults receiving meals-on-wheels experience an improvement in health-related quality of life and muscle strength, being involved in their own meals in a rehabilitation program compared to usual community aged care including receiving meals-on-wheels.

The cluster design is chosen primarily to avoid contamination, since the assigned Health Care Staff and Registered Dieticians receiving additional training could not be expected to treat individual residents differently; respectively the intervention and the control group, by preference of the older person. Also, the cluster design is chosen due to practical reasons, in order not to conflict with other nutritional projects and initiatives in the participating municipality.

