### Trial design

This study is a cluster randomized trial where clusters are a total of five community aged care areas in The City of Odense allocated into groups of two clusters. The two clusters are 1) the group of older adults being involved in own meals in a rehabilitation program (Intervention) (*n* = 3) and 2) usual care (Control) (*n* = 2). In the City of Odense there are 33,800 citizens above 65 years of age, and totally residents receiving support at home are 5453 (18+ years of age). 1477 citizens (18+ years of age) are receiving meals-on-wheels.

The intervention in the study consists of two parts (see below) targeted at individual participant level, and to separately investigate the two parts of the intervention a pre- and post-intervention comparison will be made.

An overview of the trial is presented in Fig. 1 Design of the study and flow of participant.

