### Participants

This study will use two sets of eligibility criteria, respectively for the community aged care areas (clusters) and the individual participants.

Community aged care groups (clusters): The citizens who need health care in The City of Odense are placed in a total of five community aged care areas. Excepted are those suffering from severe dementia, brain injury and mental illness, who receive special health care treatment outside the community aged care areas. All five community aged care areas will randomly be assigned into two clusters. The Intervention cluster consists of three community aged care areas: Dalum, Tagtaekker, and Skibhus, and the Control cluster consist of two community aged care areas: Rugaard, and Munkebjerg.

Inclusion and exclusion criteria for the individual participants:Inclusion criteriaCommunity-dwelling older adults (65+ years of age)Receiving meals-on-wheels (at least one time per/week) from the municipal supplier at the time of recruitmentLive in The City of OdenseExclusion criteriaModerate/severe dementia assessed by the community Health Care StaffBeing deaf and/or not understand the language of DanishNot being able to sign the informed consentReceiving (or likely to receive in the next 6 months) enteral tube feeding or parenteral nutrition;Participating in other project in the municipality about nutritional support in the form of dietetic adviceReceiving meals-on-wheels from a private supplier at the time of recruitmentOn an end-of-life care pathway

The reason for exclusion of older adults being deaf or not speaking Danish language is that the project has limited funding for translation into different languages, and it will not be possible to hire a deaf interpreter. It is, however, estimated by the researchers involved, that only a few will be excluded due to this reason.

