### Sample size

As this is a pilot trial the primary outcome is understanding the feasibility of implementing a large-scale trial. However, to determine sample size for sufficient power to evaluate developmental trajectories of our secondary outcome variables population estimates were derived using data from Beck et al. [42] who had the same design, population and outcome (quality of life by means of EQ-5D-3 L) as in the present study and showed a significant difference between intervention and control group in the EQ-5D-3 L follow-up score of (0.758 [0.222] versus 0.534 [0.355], (*P* = 0.001). Here it was found that the variation seen in quality of life was due to residual variation (the variation from individual to individual) and was not dependent on the clusters. Hence, with a statistical significance level of 0.05 and a power of 80% app. 53 is needed in each group. Estimating a drop-out rate of 20%, due to a longer intervention period than the former study [42], app. 130 participants are needed. This number could probably be included in approximately 10 weeks, for respectively control and intervention group.

The sample size for this trial will be compared with the actually collected samples as to estimate the required sample size for a future cluster randomized trial.

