#### Analysis

Although this is a pilot study, we do want to explore whether or not there is a difference between groups. All statistical analysis will be performed using a statistics program (SPSS) for Windows. Data will be entered in EXCEL and will subsequently be exported into SPSS software for analysis. All participants will be included in the analysis, regardless of whether they have completed the study or not. Depending on the data type and distribution t-test, Mann-Whitney U test and Chi2 test will be used to compare changes within and between the groups. The model of data analysis needs to consider the effect of clustering; thus, this study will be using effect models with the cluster treaded as a random effect.

The intracluster correlation coefficient (ICC) for quality of life will be calculated by means of ANOVA and published to assess the appropriateness of the sample size assessment in the study.

To assess the feasibility of the outcome measurements the confidence intervals (95% CI) will be calculated to interval estimate the population.

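### Comparing planned with collected numbers cannot size the future cluster trial, and an ICC from five areas cannot confirm or refute the zero-clustering assumption

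*Protocol article*

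**What the plan says.** The Background makes it part of the primary aim "to provide data to estimate the required sample size for a future cluster randomized study", and the Abstract lists assessment of sample size as a primary outcome. The Sample size section states the method: "The sample size for this trial will be compared with the actually collected samples as to estimate the required sample size for a future" cluster randomised trial.

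The same section sets the pilot's own size. It takes the EQ-5D-3L "follow-up score of (0.758 [0.222] versus 0.534 [0.355" from an earlier study, reports that the variation there did not depend on the clusters, and concludes that "with a statistical significance level of 0.05 and a power of 80% app. 53 is needed in each group". With 20% dropout this becomes about 130. No design effect is applied.

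The Analysis section adds that an ICC "for quality of life will be calculated by means of ANOVA and published to assess the appropriateness of the sample size assessment" in this study. It gives neither the time point nor whether arm is a factor. It attaches a 95% confidence interval to the feasibility of the outcome measurements and mentions none for the ICC. It also plans models with cluster as a random effect, but does not name them as the source of the ICC.

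On clusters, Trial design says "clusters are a total of five community aged care areas in The City of Odense allocated into groups of two clusters", and Participants says "The Intervention cluster consists of three community aged care areas". The word is thus used both for the areas and for the arms.

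**The concern.** The size of a cluster trial depends on the target difference, the SD, the ICC, the number analysed per area and the retention rate. Setting the planned number beside the collected number bears on recruitment and retention only. Nothing in it shows whether the planned number was the right one.

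The ICC is the one quantity the article explicitly sets aside for checking the sample size, and the assumption to be checked is that clustering is nil. Five areas give very little information on this. A near-zero estimate would be common even if clustering mattered, and it would look like support for omitting a design effect again. If the estimate also mixed the difference between arms into the variation between areas, it could mislead in the other direction.

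**Working it through.** **Inputs.** From the Sample size section: difference 0.758 - 0.534 = 0.224; SDs 0.222 and 0.355 (brackets read as SDs, an assumption); 53 per group; 20% dropout. Pooled variance = (0.222² + 0.355²)/2 = 0.0877, so SD = 0.296. From Trial design and Participants: five areas, three intervention and two control. Assumptions: two-sided 0.05; 106 analysed, 53 per arm, split as evenly as possible within arm (18, 18, 17 and 27, 26), an average of 21.2 per area.

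**The plan's own figure.** n per group = 2(z₁ + z₂)² SD²/difference².
- 80% power, SD 0.296: 2 × (1.96 + 0.842)² × 0.0877/0.0502 = 27.4, so 28.
- 80% power, SD 0.355: 39.4, so 40.
- 90% power, SD 0.355: 52.8, so 53.

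The stated 53 therefore does not follow from the stated 80% power; it matches 90% power with the larger SD. The dropout step does reproduce: 106/0.8 = 132.5, against about 130. The planned number is thus itself a doubtful benchmark for the comparison.

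**What the comparison yields.** Collected divided by planned is a recruitment and retention ratio. It contains no SD, ICC or target difference, so it cannot be turned into a required size.

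**Precision of the ICC with arm removed.** Between-area df = 5 - 2 = 3; within-area df = 106 - 5 = 101. The exact limits divide the observed F by the F quantiles and convert with ICC = (F - 1)/(F + m - 1), where m = 21.2. An estimate of 0 means F = 1. The 97.5% and 2.5% quantiles of F(3, 101) are 3.248 and 0.0717.
- Lower: F = 1/3.248 = 0.308; ICC = (0.308 - 1)/(0.308 + 20.2) = -0.034.
- Upper: F = 1/0.0717 = 13.96; ICC = (13.96 - 1)/(13.96 + 20.2) = 0.379.

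Design effect at the upper limit = 1 + 20.2 × 0.379 = 8.7. At the same area size, a base of 53 per arm could need anything from 53 to about 460, and a base of 28 from 28 to about 243. An observed 0.05 has an interval of -0.02 to 0.57.

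**How often the estimate is zero or below.** With a true ICC of 0.02, the expected F ratio is (1 + 20.2 × 0.02)/(1 - 0.02) = 1.43, and P(F(3, 101) ≤ 1/1.43) = 0.44. Simulation with the unequal areas gave 45%. With a true ICC of 0.01 the formula gives 0.52.

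**If computed at follow-up over five areas with no arm term.** The arm contrast adds 106 × (difference/2)²/4 to the between-area mean square. Take the true ICC as 0.
- Difference 0.224: added 0.332; MSB = 0.420; ICC = 0.332/(0.420 + 20.2 × 0.0877) = 0.15. Simulation: mean 0.15, 95% range 0.02 to 0.30.
- Difference 0.10: added 0.066; MSB = 0.154; ICC = 0.066/(0.154 + 20.2 × 0.0877) = 0.03. Simulation: mean 0.03.

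With the arm effect removed, the simulated mean is about 0.00 at either difference.

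**The case against.** The strongest reply is that the article condenses a fuller plan. The time point and model terms of the ICC may sit in an analysis plan that is not shown. EQ-5D-3L is measured at baseline in both arms, and a baseline ICC contains no treatment effect; neither does one with arm as a factor. This stands. A reader might infer that the ANOVA will absorb the treatment effect, but the text does not say so. It is a risk of the wording, and its size depends on follow-up data, no arm term and the true difference.

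A reader might also infer from the loose use of the word cluster that the ICC will be taken over the two arms, which would give about 0.21, all of it arm contrast. The documents do not support that. Trial design, Sequence generation and Allocation concealment mechanism all identify the clusters as the care areas.

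It is also fair to say that the pilot will produce an SD, completion ratios, numbers per area and random-effect models, so the raw material for sizing will exist. That rules out saying the aim is unattainable. It does not rescue the stated method, which uses none of these.

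Finally, all five areas in the city are already used, so the 3 degrees of freedom are a limit of the setting, and better analysis text will not narrow the interval. That is true, and it is why the ICC should not carry the decision alone. No passage says a near-zero ICC will be presented as proof that clustering can be ignored; that is a foreseeable misuse and not a stated plan.

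**Conclusion.** The point holds in two parts that do not depend on any disputed reading. First, the stated route to the future sample size does not produce one, although sizing is part of the primary outcome. Second, the ICC cannot test the assumption it is meant to test: with five areas, an estimate of 0 is compatible with values up to about 0.38, a design effect between 1 and about 8.7 at 21 per area. These figures assume 106 analysed, near-even area sizes within arms and an arm-adjusted one-way ANOVA.

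The third part is conditional. An ICC computed at follow-up without an arm term would average about 0.15 when the truth is 0 and the difference is 0.224, and about 0.03 when the difference is 0.10. The article leaves this open, so it calls for a clarification and is not a demonstrated error.

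**What to change.** In the Sample size section, replace the planned-versus-collected comparison with an explicit calculation for the future trial. It should use the pooled within-arm SD of EQ-5D-3L from the pilot, observed retention, expected area size, a stated target difference, and a table of ICCs that includes external values and the pilot's upper limit. Recruitment against plan can still be reported as a feasibility result.

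In the Analysis section, state that the ICC is computed over the five areas with arm as a fixed factor, or at baseline. Report it with a 95% confidence interval, and state that it will not be used alone to justify an ICC of zero. Use the word cluster for the areas only.

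The cost is a few lines of text and a small extra calculation from data already planned. The projected future trial may turn out larger.

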## Discussion

When designing this present study, we had to make several considerations to overcome the challenges of preparing and design a cluster randomized trial of adequate size and quality to indicate if there is any effect of community-dwelling older adults’ involvement in activities in relation to meals in a rehabilitation program. Challenges of the complexities working with the population of community-dwelling older adults in aged care can result in underrepresentation and recruitment difficulties due to different impairments such as physical and/or cognitive problems, the consent procedure and the high attrition rates of older people participating in research [43].

### Strengths and limitations of the study

The rehabilitation approach is a new area of research in the population of community-dwelling older adults and to our knowledge, there have only been performed a few randomized controlled studies of nutritional support among community-dwelling older adults receiving support at home, using involvement in activities related to meals. This study provides an opportunity to develop and refine consistent practices of older adults’ involvement in activities in relation to meals in the communities as part of rehabilitation programs.

A clear strength of this study is the workshop in the early stage of the project, which illuminated rehabilitation due to experts, collaborators e.g. Likewise, we also consider it a strength that also representatives of the older adults in Denmark participated in this work.

In designing the study, we will choose to develop a new tool to be used in the for the rehabilitation process, but instead we could have chosen to use an already validated tool for the rehabilitation process. However, we want to make sure that the main focus of the dialog is involvement in meal related activities, and we did not find any suitable tool for this purpose.

A limitation of this study is the exclusion of severe dementia, brain injury and mental illness and this could possible reduce the representativeness of our findings. This decision is made because of the nature of the rehabilitation program including involvement in meals.

Since this study do not have much funding attached we had to make some choices in designing this study. For instance, it could have been interesting to evaluate if there would be any change in the participants community care services, use of medicine, and health challenges, since this could be an expression of the effectiveness of the intervention, however due to limitations of time and access to this information this will not be included.

## Conclusions

This protocol has defined the aims and objectives of a feasibility cluster trial and has provided a detailed description of the intervention, the study design and the methods of data collection. For the subsequent pilot trial, the protocol will be used for detail planning. The result of the subsequent pilot trial will be used to design a definitive future trial. It is expected that the results of the definitive trial will inform decisions by Registered Dieticians working with rehabilitation to involve community-dwelling older adults in activities in relation to meals, Health Care Planners working with care planning in the municipalities, and professionals planning the future rehabilitation programs for older adults.

## Strengths and limitations of this study

This pilot study evaluates community-dwelling older adults receiving support at home, using involvement in activities related to meals with a rehabilitation approach, and this is a new area of research and will therefore be contributing in developing and refining consistent practices of rehabilitation programs.In planning this study, we held a workshop for experts, collaborators and representatives of the older adults in Denmark to get their opinions on the potentials of older adults’ involvement in activities in relation to meals as part of a rehabilitation program.A limitation of this study is the exclusion of severe dementia, brain injury and mental illness and this could possible reduce the representativeness of our findings.Evaluating if there would be any change in the participants community care services, use of medicine, and health challenges has been chosen not to be collected due to limitations of time and access.
